### Analysis for the secondary outcomes

To measure the sensitivity and specificity of the POC-CCA, the test results of the 1000 urines collected at the non-randomized sites at T0 will be compared to the results obtained from the reference panel (Table 5). Sensitivity of the POC-CCA is defined as the number of samples positive in the POC-CCA test divided by the total number of “true” positives (according to the results obtained from the combined panel of reference tests described in Table 5). Specificity of POC-CCA will be the number of sample negatives in the POC-CCA test divided by the total number of “true” negatives.

Additionally, women’s health-related quality of life scores will be compared between women in the intervention and in the control arms (Wilcoxon rank-sum test will be applied). A multivariate two-way fixed effects, regression model will be used to evaluate the effect of the intervention (while controlling for other factors) on women’s health-related quality of life scores. Finally, the costs of the intervention and health indicators will be used for the cost-effectiveness analysis. A decision tree model will be estimated and where the natural history of the disease will be represented by a Markov model. The model will be estimated by following standard approaches (i.e., deterministic and probabilistic analyses will be conducted). The association between women’s capacity to work and the intervention will also be estimated using the two-way fixed effects regression analysis, while controlling for observable time-varying factors.

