### Outcomes

The primary endpoints of the study are as follows:
The proportion of children showing stunted growth (height-for-age *z*-value < − 2) at 2 years of age to measure the impact of TBST on child developmentMaternal Hb at 24 months after delivery to measure the impact of TBST on maternal health

The secondary endpoints of the study are as follows:
Sensitivity and specificity of the POC-CCA test compared to a panel of reference standard tests (measured as part of the cross-sectional study at non-randomized sites)Women’s health-related quality of life, capacity to work and participate in economic activities and cost-effectiveness of the interventions

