### Sample size and statistical analysis

The sample size was calculated in relation to the primary child outcome proportion showing stunted growth at 2 years of age, for which a larger sample size is assumed to be necessary than for the maternal outcome (Hb, 2 years after delivery).

The prevalence of stunting in Madagascar is estimated to be 40% of children under 2 years of age [26]. For our sample size estimate, it was conservatively assumed that:
Twenty per cent of all children at the age of 2 years are stunted (height-for-age *z*-score < − 2)The intervention can reduce the proportion of stunted children by 50% in infected individuals, i.e. to observe that 10% of all children at the age of 2 years are stunted in the intervention arm.

In order to estimate the appropriate number of infected individuals at 9 months of age, sample sizes with power values of 80% and 90% were subsequently calculated using the OpenEpi tool [27]. For a power of 80%, at least 394 infected individuals at 9 months of age would be required and for a power of 90% 526 individuals. The design effect was assumed to be 1.9 by which the initial sample size needs to be multiplied to account for the clustered design of the study. This leads to a sample size of 749 for 80% power and 1000 for 90% power.

With an annual loss to follow-up of 10% from a visit to visit and an infant mortality rate of 4%, 86% of all mother-infant tandems are expected to present for the 9-month visit. For the 2 years visit, a loss to follow-up of around 10% between 9 months and 2 years is assumed, so that around 0.86 × 0.9 = 77.4% of all mother-infant tandems are expected to present for the 2-year visit. To correct for loss to follow-up, we use the factor 1/0.774 = 1.3. Since our analyses only focus on women infected with schistosomiasis, the number of women to be recruited needs adjusting, considering that the expected prevalence of 0.25 results in an additional inflation factor of 4 leading to an inflation factor of 1.3 × 4 = 5.2.

We hence planned to enrol 4200 eligible pregnant women in the 40 randomized cluster of the trial ensuring a power between 80 and 90% and an additional 1000 participants for the cross-sectional sub-study in the non-randomized sites. Based on the 40 randomized clusters identified for this study, an average of 105 women per cluster is needed to be recruited per cluster.

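### As worded, POC-CCA sensitivity and specificity divide test totals by reference totals, because the numerators are not restricted to samples with the matching reference status

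*Protocol article*

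**What the plan says.** The Outcomes section names the endpoint as "Sensitivity and specificity of the POC-CCA test compared to a panel of reference standard tests" and places it in the cross-sectional study at the non-randomized sites. The section Analysis for the secondary outcomes sets the material: "the test results of the 1000 urines collected at the non-randomized sites at T0 will be compared" with the reference panel. It then defines the two measures.

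- Sensitivity: "Sensitivity of the POC-CCA is defined as the number of samples positive in the POC-CCA test divided by the total number of" true positives, where true status is set "according to the results obtained from the combined panel of reference tests described in Table 5".
- Specificity: "Specificity of POC-CCA will be the number of sample negatives in the POC-CCA test divided by the total number of" true negatives.

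Neither sentence says that the counted POC-CCA results must come from samples with the corresponding reference status. The objectives, the Outcomes section, the design-figure legends and the ethics section do not add that restriction.

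**The concern.** Sensitivity is the share of reference-positive samples that the test picks up, and specificity is the share of reference-negative samples that it clears. Both are proportions within one reference group, so the numerator must be a subset of the denominator. Here it is not. A sample that is POC-CCA positive and reference negative is an error of the test, yet it counts in favour of sensitivity. A sample that is POC-CCA negative and reference positive counts in favour of specificity.

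The article did not leave the definition to the full protocol or an analysis plan. It gave one, and the one given does not measure accuracy. At stake are the estimates for the third specific objective. That objective supports a strategy in which treatment is offered on a positive POC-CCA result.

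**Working it through.** **Inputs.** From the protocol article: the two definitions above, and 1000 urine samples at T0. Assumed for illustration: true sensitivity Se, true specificity Sp, and prevalence p by the combined reference panel. The article gives no expected sensitivity or specificity and no panel prevalence for these two sites, so there is no stated figure to reproduce. One value of p used below, 0.25, matches the planning value in the sample size section ("the expected prevalence of 0.25 results in an additional inflation factor of 4"). That value serves to inflate recruitment and is not a forecast for the sub-study, so a range is shown.

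**Formulas.**

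- Standard: Se = TP/(TP+FN) and Sp = TN/(TN+FP).
- As worded: Se_w = (TP+FP)/(TP+FN) = Se + (1−Sp)(1−p)/p.
- As worded: Sp_w = (TN+FN)/(TN+FP) = Sp + (1−Se)p/(1−p).

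**When a value becomes impossible.**

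- Se_w − 1 = (FP−FN)/(TP+FN).
- Sp_w − 1 = (FN−FP)/(TN+FP).

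The two differences have opposite signs. If FP and FN differ, exactly one measure exceeds 100%. If they are equal, both are 100%.

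**Numbers for N = 1000, Se = 80%, Sp = 90% (assumed).**

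| p | TP | FP | FN | TN | Sensitivity as worded | Specificity as worded |
|---|---|---|---|---|---|---|
| 0.10 | 80 | 90 | 20 | 810 | 170/100 = 170% | 830/900 = 92.2% |
| 0.25 | 200 | 75 | 50 | 675 | 275/250 = 110% | 725/750 = 96.7% |
| 0.50 | 400 | 50 | 100 | 450 | 450/500 = 90% | 550/500 = 110% |

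The standard formulas return 80% and 90% in every row. Which measure passes 100% depends on prevalence.

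**Second accuracy pair.** With Se = 90%, Sp = 80% and p = 0.25, the counts are TP 225, FP 150, FN 25, TN 600. Sensitivity as worded is 375/250 = 150%, and specificity as worded is 625/750 = 83.3%.

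**Equal errors.** A test with no information, at p = 0.25 with Se = 25% and Sp = 75%, has expected counts TP 62.5, FP 187.5, FN 187.5, TN 562.5. Both measures as worded are then 100% (250/250 and 750/750).

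**The case against.** The strongest reply is that this is loose wording and not an intended formula. The section names two standard measures, says that results are compared with the reference panel, and uses the right denominators. A short phrase such as 'among these' would put both sentences right. The article also commits to STARD reporting, which makes deliberate use of a non-standard ratio unlikely. And the error tends to reveal itself: an analyst who applied the text literally would almost always see a value above 100%, or two values of exactly 100%.

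Most of this stands, and it limits the weight of the point. It does not remove it. The same gap occurs in both sentences, nothing elsewhere in the article closes it, and the measure that stays below 100% is also too high while looking believable (96.7% against a true 90% in the 25% row).

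Three stronger readings are tempting, and the article does not support them.

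- A reader might infer that both measures are inflated most when specificity is poor. That is true of sensitivity only. The excess in specificity, (1−Se)p/(1−p), does not involve Sp: at p = 0.25 it is 6.7 points in the 80%/90% example and 3.3 points in the 90%/80% example, where specificity is worse.
- A reader might take 25% as the plan's prevalence for the sub-study. It is a recruitment planning value, and the 50% row shows that the pattern reverses at another prevalence.
- A reader might expect inflated estimates to be published unnoticed. For the reason just given, that is not the likely course.

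**Conclusion.** The point holds on the text as written. The stated definitions compare the totals of the test with the totals of the reference and do not measure agreement within reference status. The algebraic result rests on no assumption: one of the two measures exceeds 100% unless FP = FN, and then both equal 100% regardless of accuracy. The size of the error does rest on assumptions. At assumed true values of 80% and 90%, sensitivity as worded ranges from 170% to 90% and specificity as worded from 92.2% to 110%, as prevalence goes from 10% to 50%.

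It is best read as a probable wording error in the definition of one secondary endpoint, confined to the non-randomized sub-study. The comparisons of stunting and maternal haemoglobin in the 40 randomized centres are unaffected. It is worth correcting because the definition is explicit, wrong and easily put right.

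**What to change.** Replace the two defining sentences with:

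- Sensitivity = number of samples positive on both POC-CCA and the combined reference panel, divided by the number of all samples positive on the reference panel.
- Specificity = number of samples negative on both POC-CCA and the combined reference panel, divided by the number of all samples negative on the reference panel.

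In the 25% example these give 200/250 = 80% and 675/750 = 90%, and neither can leave the range 0 to 100%. The cost is two sentences. Sampling, laboratory work, sample size and trial conduct do not change. If a full protocol or analysis plan repeats the wording, it should be changed there too.

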**Table 3 Tab3:**
[figure not shown]
Scheme of scheduled visits. T0 mothers enrolment at 5^th^ or 6^th^ month of pregnancy pregnancy; T1 pre-delivery follow up at the 8^th^ month of pregnancy; T2 delivery follow up at birth and inclusion of children; T3 follow up 9 month after delivery; and, T4 final follow up 24 months after delivery

T0: mother’s enrolment during the 5th or 6th month of pregnancy. Haemoglobin is measured on-site using the Hemocue® system, and a urine sample is being collected (≥ 25 ml). In the TBST intervention arm, the POC-CCA to test for schistosomiasis infection is done on-site. Women who test positive are offered (40 mg/kg) PZQ treatment. Additional samples (Table 4) are being collected at the non-randomized sites for the cross-sectional sub-study to assess the sensitivity and specificity of the POC-CCA test against a panel of reference tests described in Table 4.T1: 1st follow-up, 8th month of pregnancy. Haemoglobin is measured on-site by means of the Hemocue® system.T2: 2nd follow-up, delivery and child enrolment. The case report form (CRF) is completed. The newborns are included, unless the mother decides to withdraw her/him from the study. Weight and height of the newborns are measured.T3: 3rd follow-up, 9 months after delivery/birth. Haemoglobin is measured for all women using the Hemocue® system. Height and weight are measured for all children. A urine sample is being collected (≥ 25 ml) from all mothers and children. In the TBST intervention arm, the POC-CCA to test for schistosomiasis infection is being performed on-site for the mother and child. To test-positive mothers, a 40 mg/kg dose of PZQ treatment is offered. Test-positive children are treated with 300 mg.T4: 4th follow-up, 24 months after delivery/birth. Haemoglobin is measured for all mothers on-site using the Hemocue® system. Height and weight are measured for all children. A urine sample is being collected (≥ 25 ml) from all the women and children. In both arms, the POC-CCA test for schistosomiasis infection is being performed on-site for the mothers and children. All positive women and children are offered 40 mg/kg and 300 mg PZQ treatment, respectively.

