**Table 5 Tab5:**
[figure not shown]
Testing scheme by randomization group. The UCP-LF antibody assay will be performed at the designated laboratory on all the samples collected at T0 from the women attending the visit at both intervention and control training centres. The maternal Hb will be measured at the CSB from all the women in all the sites attending T0, T1, T3 and T4 visits. The UCP-CF CAA and the UCP-LF CAA assays will be performed at the designated laboratory on all the samples collected at T0 from all the women in all the sites and at T3 from all the children in all the sites. The POC-CCA test will be performed for all the women attending the T0, T3 and T4 visits and for all the children attending T3 and T4 visits at the CSB belonging to the intervention group. The POC-CCA test will be also performed at the designated laboratory on all the samples collected at T0 from all the women in all the sites and at T3 from all the women and children in all the sites. PCR will be performed at the designated laboratory on all the samples collected at T0 from the women attending the visit at both intervention and control training centres. Microscopy will be performed at the designated laboratory on all the samples collected at T0 from the women attending the visit at the intervention training centre (one of the two non-randomised centres)

Information on women’s health-related quality of life is collected at T0, T1, T3 and T4 in a sub-sample of women enrolled at the non-randomized centres. Information on health system resources used for TBST is collected in all the facilities by means of a simple questionnaire administered to nurses involved in the intervention.

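### The POC-CCA sensitivity and specificity formulas use the wrong numerators, and the reference panel is placed in two different tables, neither of which is shown to exclude POC-CCA or the antibody assay

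*Protocol article*

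**What the plan says.** POC-CCA accuracy against a reference panel is a secondary endpoint (Protocol article, Outcomes). It is measured at the two non-randomised centres. Under Analysis for the secondary outcomes, "the test results of the 1000 urines collected at the non-randomized sites at T0 will be compared to the results obtained from the reference panel".

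That section then gives two formulas:
- Sensitivity is the count of POC-CCA-positive samples over the total of true positives, where true status is set by the "combined panel of reference tests described in Table 5".
- Specificity is the "number of sample negatives in the POC-CCA test divided by the total number of “true” negatives".

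The panel is located differently elsewhere. The T0 entry of the Data collection plan says that the test is assessed "against a panel of reference tests described in Table 4". The Fig. 3 legend refers to Table 3 for the sub-study tests.

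The Table 5 legend describes a testing scheme by randomisation group. It covers maternal Hb, CAA assays, PCR and microscopy, and also these two entries: "The UCP-LF antibody assay will be performed at the designated laboratory on all the samples collected at T0" and "The POC-CCA test will be also performed at the designated laboratory". The Table 4 legend likewise lists POC-CCA (on urine) and an antibody assay (on serum).

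**The concern.** Sensitivity is the share of reference-positive women whom the test detects, so its numerator must be the POC-CCA positives among them. The stated numerator adds every false positive. The stated specificity numerator likewise adds every false negative. Both quantities are therefore overstated whenever the test makes errors, and either can exceed 100%.

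The second issue is which tests decide true status. The text answers only by pointing to a table, the pointers disagree, and each caption mixes candidate reference tests with the index test, an antibody assay and Hb. An analyst working from this text could build different references and report different accuracy for the test on which the whole test-and-treat strategy rests. The article also commits to STARD reporting (Ethical considerations), for which the reference standard has to be identifiable.

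**Working it through.** The plan states no expected accuracy, so there is no figure to reproduce. The calculations below are illustrations.

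**Inputs**
- 1000 women: Analysis for the secondary outcomes.
- Prevalence 0.25: Sample size and statistical analysis. Carrying it over to the two non-randomised centres is an assumption.
- POC-CCA sensitivity (Se) 0.80 and specificity (Sp) 0.90: assumed, with 0.85/0.80 and 0.70/0.95 as a range.

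**Step 1: the formulas as written**

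There are 250 infected and 750 uninfected women. True positives are 0.80 × 250 = 200 and false negatives 50. False positives are 0.10 × 750 = 75 and true negatives 675.
- Sensitivity as written: (200 + 75)/250 = 1.10. Correct: 200/250 = 0.80.
- Specificity as written: (675 + 50)/750 = 0.967. Correct: 675/750 = 0.90.

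In general, with prevalence p, the written sensitivity equals Se + (1 − Sp)(1 − p)/p, and the written specificity equals Sp + (1 − Se)p/(1 − p). At p = 0.25 these are Se + 3(1 − Sp) and Sp + (1 − Se)/3.

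| Assumed Se / Sp | Sensitivity as written | Specificity as written |
|---|---|---|
| 0.80 / 0.90 | 1.10 | 0.967 |
| 0.85 / 0.80 | 0.85 + 0.60 = 1.45 | 0.80 + 0.05 = 0.85 |
| 0.70 / 0.95 | 0.70 + 0.15 = 0.85 | 0.95 + 0.10 = 1.05 |

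**Step 2: what follows if POC-CCA or antibody counted towards true status**

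This step uses correct numerators and adds two assumptions: any positive component makes the reference positive, and the remaining panel tests classify infection perfectly.
- *POC-CCA included, laboratory reading equal to the index reading.* Every POC-CCA positive becomes reference positive. Sensitivity is (200 + 75)/(250 + 75) = 0.846. Specificity is 675/675 = 1.00 by construction.
- *Antibody included, positive in a fraction a of uninfected women, independently of POC-CCA.* Sensitivity is (200 + 75a)/(250 + 750a), which gives 0.638, 0.538 and 0.418 for a = 0.1, 0.2 and 0.4. Specificity is 675(1 − a)/[750(1 − a)] = 0.90, unchanged.

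The pattern is the same with an imperfect panel: two other tests with sensitivity 0.90 and 0.60 and specificity 1.0, and an antibody sensitivity of 0.90, all errors independent given infection status.

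| Panel | Apparent sensitivity | Apparent specificity |
|---|---|---|
| Without POC-CCA or antibody | 0.800 | 0.891 |
| POC-CCA added | 0.851 | 1.000 |
| Antibody added, antibody specificity 0.9 / 0.7 / 0.5 | 0.638 / 0.468 / 0.379 | 0.898 to 0.899 |

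**Step 3: which tests are done at which centre at T0 (Table 5 legend)**
- PCR and antibody: both training centres.
- CAA assays and laboratory POC-CCA: all women at all sites.
- Microscopy: the intervention training centre only.

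A reference that includes microscopy would therefore have different components at the two centres.

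**The case against.** On the formulas, the best defence is that the wording is shorthand. Results are compared sample by sample, STARD reporting is promised, and nobody would publish a sensitivity of 110%. That makes the error easy to spot when it exceeds 100%. It does not make the written rule correct, and an inflated value below 100%, such as 96.7% for 90%, would not draw attention.

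On the panel, a reader might infer that the reference contains the index test and that both accuracy estimates are therefore biased. The document does not support that:
- Table 5 is captioned as a general testing scheme and includes Hb, so being listed there does not make a test part of the reference.
- Outcomes, the T0 entry and the analysis section all set POC-CCA against the panel, as something separate from it.
- Laboratory POC-CCA has an evident role as the index test. On-site testing before 24 months is confined to the intervention arm, so the T0 result at the control training centre has to come from the laboratory.
- The table bodies are not visible and may mark the reference tests.
- No any-positive rule is stated, and a combination rule may properly sit in the full protocol or analysis plan.
- Nothing says that the antibody assay enters the composite or stays positive without current infection. Even if both were so, antibody alone would leave specificity almost unchanged.

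A reader might also infer that biased accuracy would pass into the cost-effectiveness model. The article names costs and health indicators as inputs and does not mention test accuracy.

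These objections stand. They reduce the incorporation and antibody issues to conditional risks. They leave the formulas and the conflicting table references untouched.

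**Conclusion.** The numerators are wrong as stated, whatever the panel contains. The size depends on assumed accuracy and prevalence: at 0.80, 0.90 and 0.25 the written rules give 110% and 96.7% instead of 80% and 90%.

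The conflict between Tables 4 and 5 as the location of the panel is also real, and the visible text does not exclude POC-CCA or antibody from the reference. What would follow is conditional. Under an any-positive rule, including POC-CCA would force specificity to 100%. Including an antibody assay that is positive without current infection would lower sensitivity, for example to between 0.42 and 0.64 when 40% to 10% of uninfected women are antibody positive, with little effect on specificity. That either inclusion is planned is not shown.

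This is worth correcting because it defines a named endpoint and the correction is nearly free. The randomised comparison and the primary endpoints are not affected.

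**What to change.** - Define sensitivity as POC-CCA positives among reference positives, divided by all reference positives. Define specificity as POC-CCA negatives among reference negatives, divided by all reference negatives.
- Cite the same table for the reference panel in the T0 description and in the secondary analysis, and align the Fig. 3 legend.
- State that no POC-CCA reading, on-site or laboratory, enters the reference.
- Base the primary reference for current infection on PCR and CAA, which are done at both centres. Report antibody separately, and use microscopy, planned at one centre only, in a sensitivity analysis.

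The cost is revised wording and minor analysis work, with no new samples or assays.

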
## Methods

### Study objectives

The overall purpose of freeBILy in Madagascar is to integrate a POC-CCA test-based schistosomiasis treatment (TBST) into routine maternal and child primary health care programmes. The study investigates the effectiveness of the strategy for controlling schistosomiasis in young children and mothers.

Specific objectives of freeBILy in Madagascar are as follows:
To assess the impact of TBST on child development by comparing schistosomiasis-associated growth and developmental disadvantages among young children in TBST sites (intervention) to those in non-TBST sites (control)To examine the impact of TBST on maternal health by comparing schistosomiasis-associated anaemia among young mothers in TBST sites to those in non-TBST sitesTo evaluate the sensitivity and specificity of the urine-based POC-CCA test for the detection of *S. mansoni* infections in routine maternal and child primary health care programmesTo conduct an economic evaluation of the TBST strategy in comparison with the status quo, including its impact on health-related quality of life and on the capacity to perform economic activities among pregnant and lactating women

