**Fig. 3 Fig3:**
[figure not shown]
Design of the cross-sectional study. The two non-randomized CSBs Andina and Imerintsiatosika were selected as the intervention and non-intervention sites, respectively. At the 5th or 6th month of pregnancy (T0), women will be enrolled in the study and consent for their children will be asked. At T0, blood, urine and stool samples will be collected. At the end of the study, the sample will be analysed with the tests described in Table 3. At 8 months of pregnancy (T1) and 9 (T3) and 24 (T4) months after birth, urine samples will be collected. At delivery (T2), children will formally become part of the study

The units of randomization are the PHCC, called *Centres de Santé de Base* (CSB). There is a total of 23 CSBs in the Antananarivo and 49 CSBs in the Fianarantsoa study area. On the basis of the criteria listed in Table 1, 20 CSBs from the Antananarivo region (10 intervention and 10 control arms) and 20 CSBs from the Fianarantsoa region (10 intervention and 10 control arms) were selected. In addition to these 40 randomized CSBs, two non-randomized CSBs have been included in the trial: one is assigned to the intervention arm (Andina) and the other to the control arm (Imerintsiatosika). Objectives 1 and 2 are rolled out in the 40 randomized CSBs. Objectives 3 and 4 are rolled out in the two non-randomized CSB.

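### Quality of life and work capacity are compared between two non-randomised CSBs, one per arm: the Wilcoxon test measures a site difference, and the fixed-effects model cannot separate TBST from site-specific change over time

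*Protocol article*

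**What the plan says.** Under Study objectives, the fourth objective is an economic evaluation of TBST, "including its impact on health-related quality of life and on the capacity to perform economic activities among pregnant and lactating women". Under Trial design and location, the text after the Fig. 3 caption says that "Objectives 3 and 4 are rolled out in the two non-randomized CSB", and of these two centres "one is assigned to the intervention arm (Andina) and the other to the control arm (Imerintsiatosika". The Randomization section covers only the other 40 centres.

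Under Data collection plan, below Table 5, information on women's quality of life "is collected at T0, T1, T3 and T4 in a sub-sample of women enrolled at the non-randomized centres". The size of the sub-sample is not given. The next sentence says that "Information on health system resources used for TBST is collected in all the facilities".

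Under Analysis for the secondary outcomes, "quality of life scores will be compared between women in the intervention and in the control arms (Wilcoxon rank-sum test will be applied"). Then: "A multivariate two-way fixed effects, regression model will be used to evaluate the effect of the intervention". Work capacity gets the same type of regression, and there the article speaks of an association. Costs and health indicators then go into a decision tree and Markov model; the article does not say at which sites the health indicators are measured. This section mentions neither the single site per arm nor the lack of random allocation.

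**The concern.** The article fixes the data source, the test and the target of inference, and they do not fit together. With one centre per arm, anything that makes the two centres differ (wealth, distance, staffing, other illness, who attends) appears as a difference between arms. A rank test on individual women treats them as independent and counts that difference as evidence about TBST. Measuring more women makes a false positive more likely, because the site difference is then estimated more precisely.

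The regression uses repeated visits and is better protected, but it has its own gap. If one site's scores drift for local reasons between T0 and T4, the drift is indistinguishable from an effect of TBST.

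At stake is whether a difference between two places is reported as a benefit (or harm) of TBST for women's quality of life or work capacity. Both belong to the economic objective, and the Discussion says that the cost-effectiveness results are meant to support national strategies and guidelines. The primary endpoints are not affected.

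**Working it through.** **The plan's own figures.** The article gives no sample size, power or intracluster correlation (ICC) for quality of life or work capacity. Its only calculation is for stunting (20% v 10%, alpha 0.05), and it reproduces. The unpooled two-proportion formula gives totals of 394 (80% power) and 526 (90% power). Multiplying by the design effect of 1.9 gives 748.6 and 999.4, stated as 749 and 1000. None of this covers the two-site comparison, but the design effect shows what ICC the authors had in mind for stunting, from ICC = (1.9 − 1)/(m − 1):

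- m = 105 women recruited per cluster: 0.9/104 = 0.0087
- m = 105 × 0.774 = 81.3 retained: 0.9/80.3 = 0.0112
- m = 1000/40 = 25 infected per cluster: 0.9/24 = 0.0375
- m = 105 × 0.774 × 0.25 = 20.3 infected and retained: 0.9/19.3 = 0.0466

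An assumed range of 0.01 to 0.05 is therefore in line with the article's own planning. That it carries over to quality of life is an assumption.

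**Wilcoxon test.** Inputs: one site per arm (from the article), alpha 0.05 (from the article, taken as two-sided), and m women per site (assumed). The article gives 1000 women at the two sites together, so 500 per site is the ceiling under an equal split. With no intervention effect, a test that ignores site has a z statistic with variance DE = 1 + (m − 1) × ICC, so

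true type I error = 2 × [1 − Φ(1.96/√DE)].

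| m per site | ICC | DE | 1.96/√DE | True error |
|---|---|---|---|---|
| 100 | 0.01 | 1.99 | 1.389 | 16.5% |
| 100 | 0.05 | 5.95 | 0.804 | 42.2% |
| 500 | 0.01 | 5.99 | 0.801 | 42.3% |
| 500 | 0.05 | 25.95 | 0.385 | 70.0% |

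This is a large-sample formula. Simulating the Wilcoxon test itself (4000 runs, ICC 0.0112) gave 16.7% at 100 women per site and 30.0% at 250, against 17.7% and 31.4% from the formula.

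**Two-way fixed effects.** With two visits, this is a comparison of changes from T0. A constant site effect cancels in the change. What remains is site-by-time variation. Its error would have to be estimated between sites within arms, which has 2 × (1 − 1) = 0 degrees of freedom.

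To size it, take a total variance of 1, a woman-level share of 0.4, a site share of 0.0112 and a site-by-time share b (all assumed). The residual share is e = 0.6 − 0.0112 − b, and the change has DE = 1 + m × 2b/(2e) = 1 + m × b/e.

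| m per site | b | DE | Interval should be wider by √DE | Error by formula | Error simulated |
|---|---|---|---|---|---|
| 100 | 0 | 1 | 1.00 | 5% | 4.8% |
| 100 | 0.005 | 1.86 | 1.36 | 15.0% | 15.9% |
| 100 | 0.0112 | 2.94 | 1.71 | 25.3% | 24.9% |
| 250 | 0 | 1 | 1.00 | 5% | 4.8% |
| 250 | 0.005 | 3.14 | 1.77 | 26.9% | 26.7% |
| 250 | 0.0112 | 5.85 | 2.42 | 41.8% | 42.0% |

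The model keeps its error rate if the site difference is constant. It loses it under modest site-specific drift. The site-level ICC plays almost no part here; b does.

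**The case against.** The strongest reply is that the adjusted analysis is the regression and that it has a T0 baseline. That stands in part: a reader might infer that the fixed-effects model cannot separate the intervention from the site at all, and this would be wrong. A constant difference between the two sites is removed, and the simulated error then stays near 5%. Nor is its standard error invalid under every assumption. It is valid if trends at the two sites would have been parallel without TBST, but two sites cannot supply the error term needed to allow for departures from that.

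A reader might also infer that the whole economic comparison rests on the two sites. The documents do not show this. Resource use is collected in every facility, and the origin of the health indicators is not stated; they may already be meant to come from the 40 randomised centres. What does remain is that the sentence placing the economic objective at the two centres does not agree with the sentence on resource use.

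Three smaller points are fair. The article does not say which visit the Wilcoxon test uses, or whether it compares scores or changes, so it cannot be charged with ignoring T0. It plans that test for quality of life only, and for work capacity it writes of an association. And it openly describes the two centres as non-randomised; these are secondary endpoints.

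One possible defence fails. The cluster random-effects models for the primary outcomes are extended to normally distributed secondary outcomes. With one cluster per arm, however, a cluster variance cannot be told apart from the arm effect.

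**Conclusion.** The point holds for quality of life, where the data source is explicit. It holds for work capacity in so far as the fourth objective is carried out only at the two centres. Arm and site coincide, so the between-arm Wilcoxon p-value is evidence about two places. Its false-positive rate is about 16% to 42% at 100 women per site for assumed ICCs of 0.01 to 0.05. The 42% to 70% at 500 per site is an upper bound and should not be read as the expected figure, since the article says that only a sub-sample is measured.

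The fixed-effects estimate is defensible only under parallel trends. With assumed site-by-time shares of 0.005 to 0.0112, its error rate is about 16% to 42% at 100 to 250 women per site. Sub-sample size, ICC, variance shares and equal split are assumptions; the lack of site-level degrees of freedom is not. That a site difference will enter the cost-effectiveness model is a possibility the wording leaves open, not something the article states.

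**What to change.** 1. Drop the between-arm Wilcoxon p-value. Report quality-of-life scores descriptively by site and visit.
2. Present the change-from-T0 (fixed-effects) estimates for quality of life and work capacity as non-randomised and exploratory, without causal wording.
3. State the parallel-trends assumption. Show how the interval widens over a range of assumed site-by-time variance shares, for example 0.005 to 0.01 of total variance. Varying the site-level ICC would not serve, because a constant site effect cancels in the change.
4. Reconcile the statement that the fourth objective is carried out at the two centres with the collection of resource use in all facilities. State that the health effect of TBST in the cost-effectiveness model comes from the cluster-adjusted results of the 40 randomised centres, with the two sites supplying only utility values.

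The cost is a change of wording and a weaker claim on quality of life and work capacity. No new data are needed. Recruitment has closed, so T0 scores can no longer be collected at the randomised centres.
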